**Analysis of the secondary variables**

(1)Neutralizing antibody titers against SARS-CoV-2 on day 40

The geometric mean of the neutralizing titers among PPS cases on day 40 will be calculated. Additionally, the geometric mean ratio of the neutralizing titer on day 40-post immunization with the second dose of BNT162b2 mRNA to the geometric mean value and the 95% confidence interval calculated in the previous study (“*Study on the changes in antibody titers by vaccination with a novel coronavirus vaccine*”) will be used; the geometric mean of the neutralizing titer on day 40 and day 0 will be calculated for the test drug-inoculated cases among the PSS cases.

Additionally, the geometric mean of neutralizing antibody titers in non-vaccinated subjects on day 40 will be calculated to compare with that in KD-414 inoculated subjects.

(2)IgG-S on days 7 and 40 post-inoculation(3)IgG-N on days 7 and 40 post-inoculation(4)IgM-S on days 7 and 40 post-inoculation(5)Th1 and Th2 responses against SARS-CoV-2 on day 7 post-inoculation(6)QuantiFERON SARS-CoV-2 test on days 7 and 40 post-inoculation

Similar analyses as in primary endpoint analysis and analysis of the secondary variables (1) will be performed for the above six items. However, for the Th1 and Th2 endpoints, the analysis will be performed on data collected on day 7 post-inoculation.

(7)Among the PPS cases, the number and percentage of COVID-19 cases in the vaccinated and unvaccinated groups will be calculated.

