**Secondary endpoint**

<Immunogenicity>

(1)Titers of neutralizing antibodies against SARS-CoV-2 on day 40 post-inoculation(2)IgG antibodies against SARS-CoV-2 spike protein (IgG-S) on days 7 and 40 post-inoculation(3)IgG antibodies against SARS-CoV-2 nucleocapsid protein (IgG-N) on days 7 and 40 post-inoculation(4)IgM antibodies against SARS-CoV-2 spike protein (IgM-S) on days 7 and 40 post-inoculation(5)Th1 and Th2 responses against SARS-CoV-2 on day 7 post-inoculation(6)QuantiFERON SARS-CoV-2 RUO test on days 7 and 40 post-inoculation

<Efficacy>

(1)COVID-19 incidence till day 40 post-inoculation

<Safety>

(1)All adverse events occurring between days 0 and 40 post-vaccination, deaths due to adverse events, serious adverse events other than death, significant adverse events, and severe (Grade 3 or higher) adverse events(2)Physician-reported outcomes
①Specific local adverse events *1②Specific systemic adverse events *2③Unspecified adverse events *3
(3)Maximum body temperature from day 0 to day 6 post-inoculation(4)Subject-reported outcomes

*1 Specific local adverse events: erythema, swelling, induration, and pain at the injection site between day 0 and day 6 post-inoculation.

*2 Specific systemic adverse events: fever (body temperature of ≥37.5 °C, if present), headache, malaise, nausea, and myalgia between day 0 and day 6 post-inoculation

*3 Unspecified adverse events: Adverse events that do not fall into the category of specified adverse events between day 0 and day 6 post-inoculation are classified as unspecified adverse events. Erythema, swelling, induration, and pain at the injection site, pyrexia, headache, malaise, nausea, and myalgia at day 7 post-inoculation are defined as non-specified adverse events.

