**Statistical analysis**
**items**

**Analysis sets**

**Study protocol-adapted analysis set (per-protocol set; PPS)**

Among the enrolled participants, subjects associated with major protocol failure and those in whom blood sampling for titration on day 7 post-immunization cannot be performed are excluded.

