**Safety set**

All patients who received KD-414 will be included.

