**Data handling**

In case of any doubt regarding the handling of data during data collection or analysis, the principal investigator and the statistical analysis manager will decide how to proceed after discussion. No imputation is performed for the missing data. Details, including handling outliers, are specified in the statistical analysis plan.

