**Primary endpoint analysis**

Primary analysis

The geometric mean of the neutralizing antibody titers will be calculated for PPS cases on day 7 post-inoculation. Meanwhile, the geometric mean ratio of the neutralizing antibody titer at day 7 post-BNT162b2 mRNA vaccination to the geometric mean value and the 95% confidence interval calculated in the previous study (“*A survey of vaccine-induced COVID-19 antibody titer to verify temporal change*”: NCGM Ethical Review Board Approval Number: NCGM-A-004175-04) will be used.

Secondary analysis for the primary endpoint
(1)The geometric mean of the neutralizing antibody titer on day 7 against day 0 will be calculated for PPS cases. Additionally, the geometric mean of neutralizing antibody titers in non-vaccinated subjects on day 40 will be calculated. The geometric mean ratio of neutralizing antibody titers in vaccinated subjects to that in non-vaccinated subjects among PPS cases will also be calculated.(2)The percentage of cases in which the geometric mean ratio of neutralizing titers on day 7 to those on day 0 was ≥4 will be calculated.(3)Subgroup analyses will be performed on the following items for test drug-vaccinated and non-vaccinated cases among PPS cases:

▪Work history (presence or absence of work-related contacts)▪Sex (male/female)▪Age (below or above the median)▪Medical history▪Interval between the third dose and the second dose of the BNT162b2 mRNA vaccine.▪By variant
(4)Among PPS cases, the geometric mean neutralizing antibody titer on day 7 will be calculated for unvaccinated cases. Additionally, if the non-vaccinated subject received the third dose of other vaccines, the geometric mean of neutralizing antibodies on day 7 after the third dose of other vaccines will be calculated.(5)Among PPS cases, the geometric mean neutralizing antibody titers on day 7 will be calculated for unvaccinated and vaccinated cases and compared using the Wilcoxon rank-sum test. Additionally, the geometric mean ratio of neutralizing antibodies on day 7 post-third dose of other vaccines against the vaccinated subject and the 95% confidence interval will be calculated for non-vaccinated subjects.

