**Analysis of safety endpoints**

The following safety endpoints will be summarized for the safety analysis set:(1)Compilation of the incidence of all adverse events occurring between day 0 and day 40, deaths due to adverse events, serious adverse events other than death, significant adverse events, high-severity (Grade 3 or higher) adverse events, and causal relationship to study drug(2)Physician-reported outcomes
Incidence, severity, days to onset, duration, incidence by dose, and causal relationship to study drugs of specified local adverse eventsIncidence, severity, days to onset, duration, incidence rate by dose, and causal relationship to study drugs of specified systemic adverse eventsIncidence, severity, days to onset, duration, incidence by dose, and causal relationship to study drugs of unspecified adverse events
(3)Calculation of summary statistics for maximum body temperature from day 0 to day 6 post-inoculation for each test drug(4)Subject-reported outcomes

The following analyses will be conducted for the outcome measures in the health observation diary completed by the study subjects.

The number and percentage of patients with symptoms of redness, swelling, induration, and pain during the 7-day period. A summary statistic is calculated for the maximum value in the case with the maximum diameter reported for redness and induration.In case of subjective symptoms and objective findings, the number and percentage of subjects with symptoms in the 7-day period will be calculated. In addition, a contingency table will be generated for the most common symptoms throughout the 7-day period.The number and percentage of subjects who used antipyretics will be calculated.

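### COVID-19 incidence is tabulated only in the per-protocol set, so a first-week case who misses the day-7 blood sample drops out of the efficacy endpoint

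*Protocol article*

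**What the plan says.** Under Secondary endpoint, the protocol article lists one efficacy item: "COVID-19 incidence till day 40 post-inoculation". Item (7) of Analysis of the secondary variables gives its analysis: "Among the PPS cases, the number and percentage of COVID-19 cases in the vaccinated and unvaccinated groups will be calculated". No other analysis of this endpoint is stated.

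The PPS definition starts from enrolled participants and removes two kinds: "subjects associated with major protocol failure", and "those in whom blood sampling for titration on day 7 post-immunization cannot be performed are excluded". Tables 1 and 2 allow one day either side for the day-7 visit. Under Data handling: "No imputation is performed for the missing data".

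The only other analysis set is the safety set: "All patients who received KD-414 will be included". It supports the safety summaries, including: "Compilation of the incidence of all adverse events occurring between day 0 and day 40". Non-vaccinated participants are not in it, and Table 2 schedules blood sampling for them but no adverse event observation.

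**The concern.** A per-protocol set tied to the day-7 sample suits a day-7 titre, which cannot be analysed without that sample. A count of COVID-19 cases needs no serum. Carrying the same set over to incidence makes inclusion depend on something that happens about a week into the outcome window, and COVID-19 itself is a plausible reason for missing the visit. Anyone lost in this way is by definition a case, so the group's incidence is pushed down. Because the two groups are set side by side, the comparison can move in either direction, depending on which group loses the case.

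**Working it through.** **Plan's own figure.** The document gives no expected incidence, power or sample size for this endpoint. Its only design figures are in Table 5, for the titre hypothesis. A one-sample t calculation (margin log10 0.67, one-sided 0.025, true difference 0) gives 34/39/45 for SD 0.35 and 44/50/58 for SD 0.40, matching Table 5. Those figures are unaffected.

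**Tracing one early case.**
1. COVID-19 on, say, day 4 is inside the endpoint window (day 0 to day 40).
2. If the participant attends on day 6 to 8, the sample is taken and the case counts.
3. If not, the PPS definition removes the person, and item (7) counts neither the case nor the participant.
4. A KD-414 recipient remains in the safety set, where the illness can be listed as an adverse event, outside the efficacy endpoint.
5. A non-vaccinated participant is in neither the safety set nor the PPS.

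Step 5 assumes that the day-7 rule applies to non-vaccinated participants. The rule speaks of immunization, which they did not receive, so its application to them is unclear. Table 2 does schedule a day-7 sample for them, and item (7) treats them as members of the PPS.

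**Share of cases at risk.** Assumption: constant risk over 40 days. Formula: day of visit / 40.
- Visit on day 6: 6/40 = 15%
- Visit on day 7: 7/40 = 17.5%
- Visit on day 8: 8/40 = 20%

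**Share of cases lost.** Multiply by the probability that an early case misses the draw. The documents do not give it, so a range is shown.

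| Probability of missing the draw (assumed) | Share of all cases lost |
|---|---|
| 25% | 3.75% to 5% |
| 50% | 7.5% to 10% |
| 100% | 15% to 20% |

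**Effect of one lost case.** Inputs from Target sample size and rationale: 60 KD-414 recipients and 97 in total, so 97 - 60 = 37 non-vaccinated if both targets are met. Case counts are assumed.

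| Group | Cases | All enrolled | One early case lost |
|---|---|---|---|
| KD-414 | 1 | 1/60 = 1.7% | 0/59 = 0% |
| KD-414 | 3 | 3/60 = 5.0% | 2/59 = 3.4% |
| Non-vaccinated | 1 | 1/37 = 2.7% | 0/36 = 0% |
| Non-vaccinated | 3 | 3/37 = 8.1% | 2/36 = 5.6% |

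With three cases in each group, the incidence ratio (KD-414 to non-vaccinated) is (3/60)/(3/37) = 0.62. It becomes (2/59)/(3/37) = 0.42 if a recipient's case is lost, and (3/60)/(2/36) = 0.90 if a non-vaccinated case is lost.

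**Likely number lost.** With three cases in a group, the upper bound is 3 × 0.20 = 0.6 cases. The realistic outcome is zero or one.

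**The case against.** The strongest reply is that little hangs on this. The endpoint is a secondary count and percentage with no test, in a non-randomized study that the protocol calls exploratory and in which it considers a study of disease prevention impractical. Infection excludes nobody; only a missing sample does, and the link between the two is inferred. The sample-size section plans 60 recipients to obtain 58 titres, so it expects only about two missing samples from all causes. A recipient's early case would still be visible among adverse events. All of this stands and limits the weight of the point. It does not give the lost case a place in the efficacy count, and it does not help non-vaccinated participants.

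A reader might infer three stronger things that the document does not support.

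- *That a fifth of cases will be lost.* Under constant risk, 20% is reached only if the visit falls on day 8 and every early case misses the draw.
- *That the primary titre analysis pools non-vaccinated participants.* The wording, "The geometric mean of the neutralizing antibody titers will be calculated for PPS cases on day 7 post-inoculation", does not restrict the set to recipients. But it is tied to inoculation, and the sample-size section assigns the main hypothesis to the 60 recipients. The same unqualified phrase is also used for the day-7 to day-0 comparison, which non-vaccinated participants cannot enter: Table 2 gives them no day-0 draw, and their stated total of 33 mL equals 19 + 14 mL from the two later visits. Recipients are meant.
- *That the day-40 titre analyses are wrong because they use the same set.* Keeping one population across the immunogenicity time points is a legitimate choice, and few participants are affected.

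**Conclusion.** The point holds in a narrow form. The document fixes a 40-day clinical endpoint in a set that requires a day-7 blood sample, so first-week cases who miss that sample are lost from the efficacy count, and no other set restores them. About 15% to 20% of cases are at risk, if risk is constant over the 40 days; a front-loaded risk would raise that share and a late wave would lower it. The actual loss is probably zero or one case, which can still change a group's incidence visibly or reduce it to zero. No primary conclusion and no sample size is affected. It is a minor improvement to a secondary, descriptive endpoint.

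**What to change.** In item (7) of Analysis of the secondary variables, count COVID-19 cases from day 0 to day 40 in all KD-414 recipients (the safety set) and in all enrolled non-vaccinated participants. Keep the PPS tabulation as a supporting analysis, and state there whether the day-7 sample rule applies to non-vaccinated participants. Leave the PPS as it is for the titre endpoints.

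The cost is a change of wording in the protocol or the statistical analysis plan. Sample size, visits and blood sampling stay the same.

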**Analysis of safety endpoints**

The following safety endpoints will be summarized for the safety analysis set:(1)Compilation of the incidence of all adverse events occurring between day 0 and day 40, deaths due to adverse events, serious adverse events other than death, significant adverse events, high-severity (Grade 3 or higher) adverse events, and causal relationship to study drug(2)Physician-reported outcomes
Incidence, severity, days to onset, duration, incidence by dose, and causal relationship to study drugs of specified local adverse eventsIncidence, severity, days to onset, duration, incidence rate by dose, and causal relationship to study drugs of specified systemic adverse eventsIncidence, severity, days to onset, duration, incidence by dose, and causal relationship to study drugs of unspecified adverse events
(3)Calculation of summary statistics for maximum body temperature from day 0 to day 6 post-inoculation for each test drug(4)Subject-reported outcomes

The following analyses will be conducted for the outcome measures in the health observation diary completed by the study subjects.

The number and percentage of patients with symptoms of redness, swelling, induration, and pain during the 7-day period. A summary statistic is calculated for the maximum value in the case with the maximum diameter reported for redness and induration.In case of subjective symptoms and objective findings, the number and percentage of subjects with symptoms in the 7-day period will be calculated. In addition, a contingency table will be generated for the most common symptoms throughout the 7-day period.The number and percentage of subjects who used antipyretics will be calculated.

**Interim analysis**

No interim analysis will be performed in this study.

**Procedures for changing the original analysis plan**

If there are changes from the original statistical analysis plan, the study plan or statistical analysis plan should be revised and explained in the clinical study report.

**Final analysis**

Analysis will be performed after fixation of the case for which data are available. The statistical analysis manager will produce the analysis report and submit it to the principal investigator.

Once the data until day 40 are fixed, they will be analyzed. When a booster vaccination at public expense is implemented, data until day 40 will be collected again and analyzed after data fixation.

**Adverse events and diseases**

**Definition of adverse events**

An adverse event is an unfavorable symptom, sign, disease, or laboratory abnormality in the study subject, which may or may not be related to the test vaccine. Adverse events are defined as those occurring on or after day 0 (day of vaccine administration).

**Definition of disease**

The adverse events suspected to be attributable to the test vaccine or procedure are classified as “diseases.” The disease should be related to the drugs or procedure used in the study. The investigator or sub-investigator will determine the causal relationship based on the evaluation shown in “Causal relationship between KD-414 and adverse events”, below.

**Defining serious adverse events**

Serious adverse events are defined by the investigator or sub-investigator (hereafter referred to as the “investigator” or “sub-investigator”) based on the following criteria:Leading to deathRequiring admission to a medical institution or prolongation of hospital stay for treatmentLeading to disabilitySerious according to 1–3Congenital disease or abnormality in later generations

Additionally, adverse events that are non-fatal, non-life-threatening, and do not require hospitalization may be considered “serious”. Serious adverse events are those that are judged to be important medical events that may put the subject at risk or require treatment or surgery to avoid the occurrence of the event. However, hospitalization for examination purposes and prolongation of hospitalization for examination purposes scheduled before participation in the study are not considered adverse events.

**Measures to be taken in case of adverse events**

(1)In case of an adverse event, the investigator will consider necessary medical treatment to ensure the safety of the subject(2)The investigator should inform the subject when medical treatment is required.(3)The investigator will confirm the resolution or stabilization of adverse events.

**Causal relationship between KD-414**
**and adverse events**

The causal relationship between all adverse events and KD-414 will be determined by the physicians enrolled in the study. The judgment should be based not only on the temporal relationship with the inoculation of KD-414 but also on the underlying disease course, complications, concomitant medications, research procedures, accidents, and other external factors. Causality will be judged and recorded according to the following criteria:**It is reasonable or possibly reasonable to attribute the adverse events to the research procedures or KD-414 inoculation.**

Undeniable causal relationship: the decision should be made according to the following criteria irrespective of whether adverse events are known to occur in the clinical study or during vaccination:➢There is a temporal relationship between studies.➢No other cause is shown, and a causal relationship to KD-414 cannot be ruled out.
Not related; judged according to the following criteria:
➢Not reasonable to attribute the adverse events to research procedures or KD-414 inoculation➢Show no temporal relationship➢Can indicate other causes

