**Individuals requiring caution about vaccination**

Patients who exhibit the pathological conditions listed below will be carefully monitored through medical examination, and their participation in the study will be considered. The patients will be informed about the aims and endpoints of the study, as well as adverse reactions. Informed consent will be obtained considering their health status and constitution before vaccination.

(1)Individuals with underlying diseases, such as cardiovascular disease, kidney disease, liver disease, hematological disease, developmental disorder, respiratory disease, and diabetes mellitus.(2)Individuals who have experienced fever within two days of vaccination or who have had suspected allergy symptoms, such as a generalized rash (not applicable if it is confirmed that the causative ingredient is not included in KD-414)(3)Individuals with convulsions in the past.(4)Individuals who may be allergic to any of the ingredients of KD-414 (thimerosal).

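### The causality criteria contradict their own heading and give no determinate class to a well-timed event for which another cause is also shown

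*Protocol article*

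**What the plan says.** The protocol article, under Causal relationship between KD-414 and adverse events, uses two classes.

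- **Heading of the related class:** "It is reasonable or possibly reasonable to attribute the adverse events to the research procedures or KD-414 inoculation".
- **Related criteria:** "There is a temporal relationship between studies" and, as a separate item, "No other cause is shown, and a causal relationship to KD-414 cannot be ruled out".
- **Not-related criteria:** "Not reasonable to attribute the adverse events to research procedures or KD-414 inoculation"; "Show no temporal relationship"; "Can indicate other causes".

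No third class exists, and neither list says whether all items must hold or one is enough. The lead-in asks for a judgment that weighs timing together with disease course, concomitant medication, study procedures and other external factors.

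Definition of disease then uses this judgment: "The adverse events suspected to be attributable to the test vaccine or procedure are classified as" diseases, with causality to be decided by the criteria above. The disease class drives the reports in Table 9 and the text around it. Causality is also tabulated in Analysis of safety endpoints, overall and for specified local, specified systemic and unspecified events.

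**The concern.** The heading admits an event once attribution is possibly reasonable. The second related criterion withdraws that when another cause is shown, even if KD-414 cannot be excluded, because the two conditions inside that item are joined by an explicit and. The same fact, another cause, appears again as a ground for not related. So the heading and the criteria below it give different answers for a case that is bound to occur, such as fever or malaise soon after vaccination in someone with a concurrent illness.

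Two outputs depend on the answer: the related counts in the safety tables, and the disease reports to the Review Board and, for the specified categories, to the MHLW and PMDA. The design gives little protection against inconsistent attribution. The study is open-label and single-arm, the safety set contains only KD-414 recipients, and Table 2 schedules no adverse-event observation for the non-vaccinated. The investigator's call therefore carries the attribution, for a product that the protocol itself describes as unapproved and without adequate vaccination experience.

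There is a second, smaller mismatch. The heading and Definition of disease cover study procedures as well as the vaccine, but the second related criterion names only KD-414. An event caused by blood sampling would fail it.

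**Working it through.** No sample size, power or event count is involved, so the check is logical.

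**Test case.** Timing plausible; KD-414 not ruled out; another cause shown; attribution still possibly reasonable.

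**Criteria applied to the test case**

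| Criterion | Result |
|---|---|
| Related 1: timing | met |
| Related 2: no other cause shown, and KD-414 not ruled out | not met (first half fails) |
| Not related 1: attribution not reasonable | not met |
| Not related 2: no timing | not met |
| Not related 3: other cause can be indicated | met |

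**Four ways to link the items**

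| Reading | Related needs | Not related needs | Class of the test case |
|---|---|---|---|
| 1 | all items | any item | not related |
| 2 | all items | all items | neither |
| 3 | any item | all items | related |
| 4 | any item | any item | both |

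Only reading 3 gives the single answer that the heading calls for. It does so at a price: timing alone would then make an event related, although the lead-in says that timing is not to be the only basis.

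**Clear cases.** An event with plausible timing, KD-414 not ruled out and no other cause meets both related items and no not-related item, so it is related under all four readings. An event with no plausible timing, another cause and unreasonable attribution meets no related item and all three not-related items, so it is not related under all four. The defect is confined to mixed cases.

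**What follows from the class**

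- *Depends on it:* the causality columns of the safety tables, and disease status with the reporting attached to it (Definition of disease; Procedures for collecting, recording, and reporting information on diseases; Table 9).
- *Does not depend on it:* recording of all adverse events, tabulation of their overall incidence including serious and Grade 3 or higher events, and prompt reporting of serious events to the institution's supervisor and the Clinical Research Safety Management Office.

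**Scale.** The document gives no frequency of mixed cases, so the effect cannot be estimated. As a unit only: at the target of 60 recipients, each recipient whose sole related event is a mixed case moves the related incidence by 1/60 = 1.7 percentage points.

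**The case against.** The best defence is that the lists are supports for a medical judgment and not a checklist. The first not-related item is the negative of the heading. If it governs, with timing and other causes as evidence for or against, the scale is coherent. The label of the related class, literally undeniable, may be a translation of cannot be denied, which is inclusive. The article is condensed, and the way heading and items nest may have suffered in text extraction. Definition of disease mostly refers back to these criteria and is not a separate threshold.

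Much of this stands, and it limits the point. It does not remove it: the restrictive condition is written inside a related criterion, and the text nowhere says that the heading prevails. That the first not-related item mirrors the heading also supports reading the heading as the test for the related class.

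A reader might infer several stronger things that the documents do not support.

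- *Any event with another possible cause is classed as not related.* The text speaks of a cause that is shown or can be indicated, which is more than possible, and forced exclusion is one of four readings.
- *These events disappear from reporting.* They are still recorded and counted, and serious ones still go to the institution's supervisor and the safety office whatever the causality.
- *The bias is proven to run one way.* Reading 1 lowers the related count, but the other readings give different results.
- *The problem is concentrated in the caution group,* "Individuals with underlying diseases, such as cardiovascular disease, kidney disease, liver disease, hematological disease, developmental disorder, respiratory disease, and diabetes mellitus". Another cause may be easier to name in these people. The document does not show how often, and exclusion criterion (4) already removes those whose underlying disease is serious.

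**Conclusion.** The point holds as a contradiction and an indeterminacy. For an event with plausible timing, KD-414 not excluded and another cause shown, the heading and the criteria disagree, and the criteria themselves allow four different classifications. Such events may be left out of the related tabulations and of disease reporting to the Review Board, MHLW and PMDA. Whether and how often that would happen depends on how each investigator reads the list, and no size can be derived from the document.

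The conclusion rests on two assumptions: that the possibly-reasonable sentence heads the related class, and that the separate procedures for responding to adverse events, which the protocol cites but which are not at hand, do not override these criteria. It is a stated rule that conflicts with itself, not a detail left to another document. It deserves correction because attribution in this single-arm study rests on that rule.

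**What to change.** Reconcile the heading, the two criteria lists and Definition of disease so that the classes are complementary:

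1. State how the items in each list are linked.
2. Apply the heading's own test, for KD-414 or a research procedure, as the criterion for related.
3. Make not related the complement: attribution is not even possibly reasonable. Timing and other causes then serve as evidence for that judgment. An indicated alternative cause should not by itself make an event not related while attribution remains possibly reasonable.
4. Name research procedures alongside KD-414 in the related criterion, and carry the same wording into the case report form guidance and the disease definition.

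The cost is wording in the protocol and case report form guidance, and somewhat more events classed as related and reported. Visits, sample size and study treatment do not change.
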